### EMA and Stop-Cannabis App Tools

#### Ecological Momentary Assessment

The EMA was designed as an app for mobile phones. This application allows several daily self-assessments (e.g., five times a day for 2 weeks at different times of the study/monthly). Data are collected in response to a signal from the EMA app that occurs at various times of the day. The app has been programed to send signals (i) a fixed number of times per day at predetermined times (e.g., at bedtime) and (ii) at random (with a balance between week, weekends, and holidays, with different time intervals in daytime). Participants are also asked to complete self-assessment immediately following substance use.

The same questions are presented regardless of assessment type. There are seven questions in total:
Information relating to substance use:
○Daily use of each substance in list.○Level of withdrawal symptoms during participants’ most recent period of abstinence from 0 (not at all) to 5 (severe).○Level of craving from 0 (no urge) to 5 (extreme urge).Information relating to psychopathology:
○Level of negative affect rate using a brief version of the Positive and Negative momentary Affect Scale (PANAS) (48) adapted for EMA (32). Participants provide ratings of the extent to which they felt each emotion on a 1–5 point Likert-type scale.○Main psychiatric symptoms.Information relating to environment:
○Stressful events.○Activities: physical activity, planned activity, lone activity, social activity with peers, family activity, and online activity.

Participants will be trained on EMA use during the week prior to hospital discharge. They will be asked to respond to any signals within 1 h if possible. Consistent with other EMA protocols, participants will complete 2 days of practice data (not used for analyses), after which they will receive feedback on adequate use and compliance. Participants will then be invited to complete EMA assessments for 2 weeks, as this timeframe appears sufficient to monitor substance use (45). To limit attrition, participants will be paid 30€ for completing the baseline assessment and 10€ for each week of complete EMA data, up to a maximum possible payment of 60€ over 1 year.

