#### Statistical Methods

##### Primary Outcomes

Pearson correlations will be used to determine the strength of associations between daily substance use assessed by either EMA, or self-report questionnaire (e.g., CAST), or by clinician-report questionnaire (e.g., RECAP) during the clinical assessment at 6 months. Clinical reliability of the EMA will be endorsed if the correlations are statistically significantly higher than 0.70. Further analyses would be performed to estimate different aspects of reliability of the data collected in line with Perrez et al. (64). The severity of SUDs at baseline should predict the severity of substance use and the level of functional impairment at 1 year at least to comparable levels while using EMA data at baseline compared with traditional methods. Two simple linear regression models will be performed. For both the models, the dependent variable will be the severity of SUDs at follow-up; in one model, the independent variable will be the severity of SUDs based on EMA data (Model A), whereas in the other model, the variable will be severity of SUDs based on self- and clinician-report (Model B). The estimate of the independent variable is expected not to be lower in the Model A than in the Model B.

The dropout rate is expected to be less than 40% at 6 months and less than 50% at 12 months for both the EMA and traditional method, with no significant difference between methods. The results of the satisfaction survey will be estimated by analyzing the percentage of answers and the differences among the different categories using Chi-square analysis.

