## Discussion

### Anticipated Results

#### Primary Objectives

A degree of correlation higher than 0.70 is expected between EMA data and data collected using other methods (particularly frequency of use), in line with prior studies (46). EMA should lead to predictions regarding the course of SUDs over the 1-year follow-up (e.g., in term of persistence, severity, and functional impairment) at least as good as other methods; that would be of interest for the clinicians involved in usual care. A high level of compliance with EMA is expected, despite the relative severity of the study sample. Based on previous studies in adolescents (45, 67), participants are expected to complete a mean of more than 70% of random signals, 50% of end-of-day assessments, and 40% of both random and end-of-day assessments. Indeed, there is good evidence that EMA can be used by patients with severe psychiatric disorders (e.g., schizophrenia) or cognitive difficulties (32, 46).

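### The comparison of EMA with conventional measures as predictors of 1-year severity rests on unstandardised regression slopes, so it reflects units and spread as well as predictive value

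*Protocol article*

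**What the plan says.** The Primary Outcomes paragraph of the article's Statistical Methods sets the aim that baseline severity should predict 1-year severity of use and functional impairment "at least to comparable levels while using EMA data at baseline compared with traditional methods". For this, "Two simple linear regression models will be performed". "For both the models, the dependent variable will be the severity of SUDs at follow-up". The single predictor is an EMA-based severity score in Model A and a self- and clinician-report severity score in Model B. The comparison is then stated as: "The estimate of the independent variable is expected not to be lower in the Model A than in the Model B".

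The Anticipated Results section repeats the aim: EMA should give predictions over the year "at least as good as other methods".

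The text does not say that predictors are standardised, that both scores share a metric, or that R², correlation or prediction error is compared. No interval is attached to the comparison.

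**The concern.** The aim concerns predictive value, but the quantity named is a regression coefficient. Coefficients from two simple regressions on the same outcome can be compared as measures of prediction only if the two predictors have the same spread. Nothing in the article ensures that.

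The source measures differ in kind. The EMA section lists daily use per substance and 0–5 ratings of craving and withdrawal. The conventional side has a 6-item self-report scale (CAST), a clinician questionnaire (RECAP) and the DEP-ADO, with windows of 6, 1 and 12 months.

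The finding that EMA predicts as well as usual methods could therefore be produced, or lost, by the choice of EMA scoring. A bare ordering of two point estimates also says little at the expected number of completers.

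**Working it through.** **Plan's own figure.** The article gives no margin, power or expected coefficient for this comparison, so there is nothing to reproduce.

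**Algebra (no assumption needed).** In simple linear regression, b = r × SD(Y)/SD(X). With the same Y in the same participants,

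b_A ≥ b_B is equivalent to r_A/SD(X_A) ≥ r_B/SD(X_B).

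Multiplying the EMA score by a constant c > 0 divides b_A by c and leaves r_A and R² unchanged. Going from a proportion to a percentage (c = 100) cuts the slope a hundredfold with no change in information.

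**Inputs from the article (Sample Size).** There are 40 cases, and only cases use EMA. Retention at 1 year is 50%, so 40 × 0.50 = 20 completers.

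**Assumed inputs (none are in the article).** SD(Y) = 5; comparator SD(X_B) = 5, held fixed throughout; correlation between predictors 0.7; trivariate normal data; at least 20,000 simulated trials per row.

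**Equal validity, r_A = r_B = 0.5.** Model B slope = 0.5 × 5/5 = 0.50.

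| EMA score | Assumed SD | Model A slope | Expectation met, n = 20 |
|---|---|---|---|
| Proportion of days, 0–1 | 0.30 | 0.5 × 5/0.30 = 8.33 | about 99% |
| Mean 0–5 rating | 1.25 | 0.5 × 5/1.25 = 2.00 | about 98% |
| Days out of 14 | 4.2 | 0.5 × 5/4.2 = 0.60 | about 69% |
| Days out of 14, wider spread | 4.7 | 0.5 × 5/4.7 = 0.53 | about 58% |
| Percentage of days | 30 | 0.5 × 5/30 = 0.083 | about 2% |

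The rows with SD 0.30, 4.2 and 30 are the same score in three units (0.30 × 14 = 4.2; 0.30 × 100 = 30). Their pass rates differ only because of the units.

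**Unequal validity, n = 20.**
- EMA truly worse (0.3 against 0.6): the expectation is still met about 88% of the time as a proportion, about 14% as days out of 14 (SD 4.2) and about 0.2% as a percentage.
- EMA truly better (0.6 against 0.3): it is met only about 16% of the time as a percentage.

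**The same data compared on a scale-free measure.** With standardised slopes (equal to r here), EMA is at or above the comparator about 50% of the time under equal validity, about 2.5% when worse and about 97.5% when better, whichever unit is used.

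**Uncertainty.** Under equal validity the central 95% range of r_A − r_B is about −0.31 to +0.31 at n = 20, and −0.21 to +0.21 at n = 40. Even a scale-free ordering of point estimates therefore needs an interval.

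**The case against.** Several points on the other side have force.

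- **The article does not use the word unstandardised.** A plan not shown could standardise both scores or put both on a common frequency metric, and the emphasis elsewhere on frequency of use is compatible with that. This stands as a limit: differing units are likely, not stated. But the article did not leave the method open. It names the models, the quantity and the direction, and the estimate from a simple linear regression is ordinarily the unstandardised slope.
- **The sentence states an expectation.** The 0.70 correlation criterion in the same paragraph says when reliability will be endorsed; the regression sentence does not. A reader might infer that EMA passes or fails on this comparison. The text does not support that.
- **Validity rests mainly elsewhere.** The Outcomes section defines the validity parameter through correlation analysis, which is unit-free. A reader might infer that units decide the study's primary validity conclusion. They do not; the regressions are supporting evidence.
- **Shared method is not established.** A reader might infer that the 1-year outcome comes from the same instruments as Model B's predictor, which would favour Model B. Table 1 does repeat DEP-ADO, RECAP and CAST at 1 year, but it also lists K-SADS-PL then, and the outcome instrument is not named. The point can only be conditional.
- **The SDs are assumed.** They are, and the direction and size of any distortion in this study cannot be computed from the article. At similar spreads (SD 4.7 against 5) the distortion is small.

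**Conclusion.** The point holds as a should-fix. As written, the comparison is made on a quantity that mixes predictive value with the predictor's units and spread, and it has no measure of uncertainty. The unit dependence is algebraic. Its size is illustrative: with one fixed comparator and equal validity, from about 99% to about 2% for the same EMA information in different units, under the assumed SDs, correlations and 20 completers. If the predictors are in fact standardised or share a metric with equal spread, the unit problem disappears and only the missing interval remains. The article does not say so.

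A second, smaller gap stands on the text alone. Functional impairment at 1 year is named as a prediction target, but both models have SUD severity as their only outcome.

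**What to change.** 1. Fit both models in the same participants, namely those with baseline EMA, baseline conventional measures and the 1-year outcome.
2. Replace the comparison of estimates with standardised coefficients or R² (equivalently, the two dependent correlations with the outcome).
3. Report the A−B difference with a bootstrap 95% CI, resampling participants, and judge comparability from that interval, not from the order of two point estimates.
4. Fit the same pair of models with 1-year functional impairment as outcome. C-GAF is already scheduled at 1 year. Table 1 lists it as self-report, so it does not clearly remove a shared-reporter effect.
5. Name the instrument behind 1-year SUD severity. If it is one that also supplies Model B's predictor, state that shared method may favour Model B.

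The cost is a few sentences and a few lines of code, with no new data. The downside is a weaker claim: at about 20 completers the interval will be wide and may not settle whether EMA is comparable.

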#### Sample Size

A conservative approach was adopted for this feasibility study, which emphasizes descriptive and qualitative feedback. Consequently, based on the recommendations for pilot studies (44), we plan to include 80 participants (40 cases, 40 controls) over a 2-year inclusion period. As there are around 280 inpatient admissions per year in the Department of Child and Adolescent Psychiatry, i.e., *n* = 560 potential participants contacted at baseline during the 2 years, this will represent a 14% inclusion rate. We predict that the prevalence of SUDs will be similar to that previously reported (18). A good level of compliance with EMA and Stop-Cannabis is expected, consistent with previous studies that reported high levels of adherence (up to 80%) to similar tools in adolescents with comorbid psychiatric disorders (31, 45), and in adults with associated severe psychiatric disorders (32, 46). An acceptance rate of 80% is expected in the SUD group and 50% for the control group. A 50% retention rate at 1-year follow-up is anticipated based on previous longitudinal studies among adolescents (47). In case of a lower enrollment rate, we will either continue to enroll participants during an additional year (2019) in order to reach the intended sample size or use incentives (e.g., free participation in leisure and sport activities in groups) to encourage participant enrollment.

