### Limitations

Several limitations may preclude interpretation of our findings. As no control group for the Stop-Cannabis app is defined (i.e., subjects with cannabis use disorders without the intervention), the effectiveness of the Stop-Cannabis app to reduce or quit cannabis cannot be directly examined in our study. Furthermore, one other limitation is related to the lack of EMA assessments for the control group. The groups cannot be then compared with the EMA data. The authors choose to not use EMA assessment for the control group in order to avoid possible impact of the assessments on the behaviors [for a discussion about the reactivity effect of EMA, see Shiffman (25)]. The groups will receive, however at different time, a number of clinical assessments useful for the planned comparisons. As our study participants will be recruited during hospitalization in a university teaching hospital, the sample is likely to comprise youths with severe or resistant clinical profiles, which could limit the generalizability of our findings. In addition, the study design requires that only participants who own a smartphone are included, which is a risk for selection bias. Attrition biases may result from high dropout rates and low use of the app, but incentives and reminder phone calls will be employed to improve adherence. However, if important differences in baseline characteristics between adherent and non-adherent participants are detected, this will be further controlled by regression analyses. Finally, no firm conclusion about the benefit of the Stop-Cannabis application can be drawn from this study with regards to the lack of controlled randomized group.

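### The EMA and interview regressions (Models A and B) are compared without requiring the same participants or a common scale, so the contrast may mix measurement quality with who answered the app

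*Protocol article*

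**What the plan says.** The validity of EMA data is the second parameter under Outcomes, Primary Outcomes. Statistical Methods, Primary Outcomes gives one way to judge it: "Two simple linear regression models will be performed", both with SUD severity at follow-up as the dependent variable. The predictor is EMA-based severity in Model A and self- and clinician-reported severity in Model B. The stated expectation is that "The estimate of the independent variable is expected not to be lower in the Model A than in the Model B". The section gives no margin, scale or set of participants for this comparison.

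Other sections determine who can have each predictor:

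- **Inclusion and Exclusion Criteria; Limitations.** Only the SUD group receives the apps. Controls have no EMA.
- **Ecological Momentary Assessment.** Participants are trained before discharge, complete two practice days that are not analysed, and are then invited to respond for two weeks.
- **Initial Clinical Assessment and Follow-Up.** All participants, cases and controls, are assessed before discharge and interviewed at 6 months and 1 year.
- **Sample Size.** "we plan to include 80 participants (40 cases, 40 controls) over a 2-year inclusion period", with 50% retention at 1 year. Good compliance is expected, in line with earlier studies reporting "high levels of adherence (up to 80%) to similar tools".
- **Limitations.** "Attrition biases may result from high dropout rates and low use of the app". Regression adjustment is promised if adherent and non-adherent participants differ importantly at baseline.

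**The concern.** Two estimates can be compared as measures of the same thing only if they come from the same people and are on the same scale. Neither is required here.

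- **Participants.** A case who answers no analysable baseline prompt has no Model A predictor but does have a Model B predictor. Software that drops incomplete records model by model would then give the two regressions different participants. If the missing cases tend to be more severe, Model A covers a narrower range of severity. Its predictive strength can then look weaker even when EMA measures severity equally well.
- **Scale.** A slope from a simple regression depends on the units of its predictor. EMA and questionnaire severity have different units, so their raw slopes are not comparable, even in identical participants.

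At stake is the reading of one of the primary validity comparisons: EMA could be judged worse, or better, for reasons unrelated to its quality as a measure.

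**Working it through.** **The plan's own figure.** 80 participants out of 560 admissions is 80/560 = 14.3%, which agrees with "this will represent a 14% inclusion rate". The 80 rests on recommendations for pilot studies. No sample size or power is given for Model A against Model B, so there is nothing further to reproduce.

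**Numbers available.** Cases with a 1-year outcome: 40 × 0.50 = 20. The documents do not give the share of these with a usable baseline EMA score, so it is assumed. At 80% usable, Model A has 20 × 0.8 = 16 participants and its standard error is √(1/0.8) = 1.12 times as large. At 70% it has 14, ratio 1.20. A smaller sample alone widens the interval and does not bias the slope.

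**Scale.** Slope = r × SD(outcome)/SD(predictor). With the same r and outcome, a predictor whose SD is twice as large has half the slope. A raw-slope comparison is therefore partly a comparison of units.

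**Selective non-response, simulated.** Assumptions: 20 retained cases; both measures correlate 0.5 with the outcome and 0.7 with each other; 20% lack an EMA score; non-response is correlated with severity as shown. Model A uses those with EMA, Model B all 20. A fair comparison of two equally valid measures meets the not-lower rule in 50% of trials.

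| Link to severity | Mean r, Model A (Model B 0.48–0.49) | Rule met, correlations | Rule met, raw slopes |
|---|---|---|---|
| none | no material difference | about 50% | about 50% |
| 0.5 | 0.46 | 46% | 48% |
| 0.8 | 0.42 | 38–39% | 46% |
| 1.0 | 0.38 | 32% | 44% |

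With 40% unscorable, the correlation results are 45%, 37% and 28%. Fitting both models on the same participants restores about 50% in each of these scenarios.

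The raw-slope column depends on what non-response is tied to. The table ties it to the average of the two measured scores. If it is tied to unobserved true severity, raw slopes give 48%, 42% and 37%, and correlations 45%, 37% and 29%.

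**A second set-up.** Assumptions: reliability 0.7, true slope 0.5, raw slopes, logistic non-response, 80% usable. Mean slopes for A against B are:

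- 0.416 against 0.417 if non-response is random;
- 0.382 against 0.418 if it depends strongly on severity;
- 0.254 against 0.418 if it depends strongly on severity and on outcome.

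On the common set, Model B's slopes are 0.417, 0.379 and 0.253, matching Model A. Across usable shares of 80%, 60% and 40%, A falls below B in 53–57% of runs under severity-only dependence and in 66–80% when the outcome also matters.

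**Against sampling noise.** In the severity-only case the shift is 0.418 − 0.382 = 0.036, while the SD of Model A's slope is 0.277. The shift is 0.036/0.277 = 0.13 of an SD. When the outcome also matters it is (0.418 − 0.254)/0.258 = 0.64 of an SD.

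**Controls.** The section does not restrict Model B to cases. If 20 retained controls entered Model B only, and scored 1 SD lower than cases at both times (assumed), Model B's correlation would rise to about 0.60 and the rule would be met in about 28% of trials. At 1.5 SD it would be about 12%.

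**The case against.** The strongest reply is that the article never says the models use different participants. An analysis set is often left to the full protocol or SAP, which are not shown. That stands against any claim that EMA will be judged on a smaller, selected group. A reader might infer this, but the text supports only that it may happen. The article does, however, fix the models, predictors, outcome and rule of comparison, and that rule is not like for like as worded.

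Other replies stand in part:

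- **Compliance.** A reader might infer that the plan expects 20% of cases to lack EMA. It does not. It expects good compliance and mentions low use only as a possibility. Compliance is defined as the share of prompts completed per participant, so 80% adherence does not mean that 20% have no score. Partial responders can be scored. Training, practice days with feedback and payment make total non-response less likely, and the article expects no significant difference in dropout between methods.
- **Heavier users.** That they respond less is plausible, but the documents do not say so. Links of 0.8 to 1.0 are extreme.
- **Controls.** A reader might infer that controls enter Model B. The article does not say this, and a model of SUD severity more naturally concerns cases.
- **Adjustment.** Limitations does promise regression adjustment. It is conditional, is not part of the one-predictor models, and can neither supply missing EMA scores nor align the two sets.
- **Materiality.** The rule is an expectation in a 40-case pilot, not a pass/fail test. Even on a common set, equally valid measures meet it only about half the time.

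**Conclusion.** The point holds as a weakness in how a primary-outcome comparison is specified, not as a demonstrated bias. The two estimates need not come from the same participants or be on the same scale, and the promised adjustment does not cure either problem.

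The size cannot be known from the documents. It is nil if non-response is random. With 20% of 20 retained cases unscorable and non-response linked to severity, the chance that an equally valid EMA meets the rule falls from 50% to about 46–32% on correlations. On raw slopes it falls to about 48–44%, or as low as 37% if true severity drives non-response. It is lower still if non-response also follows the outcome. The unscorable share, the link to severity and the validity values are all assumptions. Under severity-only non-response the slope shift is small beside sampling error at this sample size. The correction is worth making because it costs almost nothing.

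**What to change.** Add to Statistical Methods, Primary Outcomes, in words such as: *Models A and B will be compared in the same SUD participants, namely those with baseline EMA severity, baseline self- and clinician-reported severity and the 1-year outcome. The difference between their standardised estimates will be given with a paired bootstrap interval. Model B in all SUD cases, and the number and baseline severity of cases without EMA, will be reported alongside.*

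The common set makes the direct comparison like for like among responders. The accompanying Model B and the description of non-responders show how far that comparison can be generalised.

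The change is to analysis wording only and needs no new data. Model B loses a few participants in the direct comparison (20 to 16 if 80% have a usable EMA score). The paired interval will be wide at that size, and the result should be read as descriptive.

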## Methods and Analysis

### Selection of Participants

#### Inclusion and Exclusion Criteria

Participants will be adolescents (11–18 years old) who are hospitalized in the Department of Child and Adolescent Psychiatry at the Pitié-Salpêtrière University Hospital between September 2016 and September 2018. The participants will be assessed at baseline. According to the presence or absence of comorbid SUDs, they will be included in either the SUDs group or the control group. The SUDs group will receive the mobile apps, whereas the control group will not. Exclusive tobacco consumption is not considered to be a criterion for inclusion in the SUDs group. Inclusion to the non-SUD control group will be made according to a match with adolescents from the SUDs group (for age, gender, inpatient unit, and time of admission). Exclusion criteria include non-French speaking, those without a personal mobile phone, lack of informed consent from parents or from the adolescents, and any mental or physical problems that interfere with participation in the study (e.g., autism with very low communication abilities, severe to profound intellectual disability, severe motor disability).

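### Non-significance with no margin cannot show similar dropout for EMA and traditional assessment in about 40 paired participants, and the 12-month figure does not fit the retention assumption

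*Protocol article*

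**What the plan says.** The Outcomes section makes dropout at 6 and 12 months a measure of acceptability, within the first of the two primary parameters. Statistical Methods, Primary Outcomes, gives the only quantified standard for it: "The dropout rate is expected to be less than 40% at 6 months and less than 50% at 12 months". These figures apply to each method separately, and the sentence then adds a condition on how the two compare: "with no significant difference between methods". No margin for the difference is stated.

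Three other statements bear on this:

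- Inclusion and Exclusion Criteria: "The SUDs group will receive the mobile apps, whereas the control group will not". EMA dropout can therefore be observed only in the SUD group. Initial Clinical Assessment and Follow-Up gives face-to-face interviews at 6 months and 1 year to everyone, so SUD participants are followed by both methods.
- Sample Size: "we plan to include 80 participants (40 cases, 40 controls) over a 2-year inclusion period". The number rests on recommendations for pilot studies, not on a power or precision calculation.
- Sample Size, on follow-up: "A 50% retention rate at 1-year follow-up is anticipated".

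**The concern.** There are two separate problems.

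The first is inferential. A comparison in about 40 people often returns a non-significant result even when one method loses many more participants than the other. With no margin, finding no significant difference cannot be read as finding similar dropout. The Clinical and Research Implications section says the results should help decide whether a randomised trial is feasible. Materially worse retention on EMA, reported as no difference, could mislead that decision.

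The second is internal consistency. Retention of 50% means dropout of 50%, and 50% is not below 50%. The planning value lies on the edge of the figure given for the primary outcome.

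**Working it through.** **Inputs.** 40 SUD cases and 40 controls (Sample Size); EMA in cases only (Inclusion and Exclusion Criteria); limits of 40% and 50% (Statistical Methods, Primary Outcomes); 1-year retention 50% (Sample Size). A two-sided 5% level is assumed: the article states p < 0.05 only for a secondary comparison. The documents do not say how many participants would drop out of one method but not the other, so a range is shown.

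**The plan's own figure.** 80/560 = 14.3%, which agrees with the stated 14% inclusion rate. There is no power or precision figure for dropout to reproduce.

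**A large excess can meet the 12-month figures.** Take visits 11/40 = 27.5% and EMA 19/40 = 47.5%. Both are below 50%.

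- Unpaired, uncorrected chi-square: pooled rate 30/80 = 0.375; SE = √(0.375 × 0.625 × 2/40) = 0.108; z = 0.20/0.108 = 1.85; p = 0.065.
- Paired, exact McNemar, with the same margins:

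| Lost to EMA only | Lost to visits only | Excess | p |
|---|---|---|---|
| 12 | 4 | 20 points | 0.077 |
| 8 | 0 | 20 points | 2 × 0.5⁸ = 0.008 |
| 5 | 0 | 12.5 points | 2 × 0.5⁵ = 0.0625 |

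The last row is the most favourable split for detection, since everyone lost to visits is also lost to EMA. An observed excess of 12.5 points is still non-significant.

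**Power of the paired comparison** (exact McNemar, n = 40, simulated; the range covers the assumed discordance):

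| True excess | Assumed discordance | Power |
|---|---|---|
| 10 points | 10% to 30% | 21% down to 13% |
| 15 points | 15% to 35% | 57% down to 27% |
| 20 points | 20% to 40% | 83% down to 44% |

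Treated as two independent groups of 40, power is 14% for 50% v 60%, 27% for 50% v 65% and 45% for 50% v 70%.

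**Precision if no difference is observed.** The paired 95% half-width is 1.96 × √(discordant count)/40. With 4 v 4 discordant it is 1.96 × √8/40 = 13.9 points; with 8 v 8 it is 1.96 × √16/40 = 19.6 points. Even identical observed rates would leave an excess of that size open under these splits.

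**The 12-month boundary.** Observing less than 50% in 40 people means at most 19 dropouts. By the binomial distribution:

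| True 12-month dropout | P(at most 19 of 40) |
|---|---|
| 50% | 0.437 |
| 45% | 0.684 |
| 40% | 0.870 |

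An 80% chance of observing less than 50% needs true dropout of about 42% or lower.

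**The case against.** The strongest reply is that the article says dropout is expected to be below these figures. It does not set a pass/fail rule. The same section does use decision language elsewhere: EMA reliability will be endorsed if correlations significantly exceed 0.70. A reader might infer that the study will formally declare the methods comparable, or will fail if 12-month dropout reaches 50%. The text supports neither inference. What remains is that this expectation is the only quantified dropout standard for a primary outcome that asks whether acceptability is satisfactory, and its between-method part says little at this size.

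The absolute limits also give some protection. A reader might suppose that EMA dropout of, say, 60% could slip through as non-significant. It could not meet the stated expectation, because it exceeds the 50% figure for EMA whatever the p-value. That is why the example above stays below 50% for both methods.

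Pairing can also help. If those lost to visits are nearly all lost to EMA too, a 20-point excess would probably be detected. This stands, and it limits the point. It does not rescue excesses of 10 to 12.5 points.

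On the boundary, 50% retention is a round figure from earlier adolescent cohorts. It refers to follow-up in general and enters no calculation. A reader might conclude that the 12-month expectation is unlikely to be met. That is too strong: the chance is a little below even at exactly 50% and well above even if true dropout is a few points lower.

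Finally, the choice of test and interval may properly sit in an analysis plan that is not shown. The point here rests on the significance wording that the article does contain.

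**Conclusion.** The point holds as a wording and interpretation problem in a primary outcome. Finding no significant difference, with no margin, is not evidence of similar dropout in about 40 paired participants. An observed 12.5-point excess is non-significant under any split, and a 20-point excess may or may not be, depending on discordance that the documents do not give. The calculations assume 40 SUD participants enrolled, each classed as dropped or retained on each method, and a two-sided 5% level.

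The mismatch between 50% anticipated retention and dropout below 50% is real, but it is a boundary inconsistency. It does not show that the study is set up to miss its own figure.

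**What to change.** 1. Remove the absence of a significant difference from the dropout expectation.
2. Report 6- and 12-month dropout for each method with 95% CIs, together with the paired difference (EMA minus face-to-face visits, in the same SUD participants) and its 95% CI, as description.
3. Make no claim of comparability unless the upper limit of that interval lies below a margin stated in advance. As a guide to scale, with 50% true dropout in both methods, one-sided 2.5%, 80% power and independent groups, n per group = (1.96 + 0.84)² × 2 × 0.25/margin². This gives 393 for a 10-point margin, 99 for 20 and 44 for 30. Pairing would change these numbers, but they show why a pilot of this size should describe and not claim.
4. Reconcile the 12-month figure in Statistical Methods with the retention assumption in Sample Size: either justify anticipated retention above 50%, or restate the 12-month expectation.

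The cost is wording only; no extra data or participants are needed. The downside is that the pilot can no longer claim that the two methods have equal dropout.
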